### Design

This clinical study was a randomized, double-blind, double control trial that tested drugs and placebo. Noninferiority (versus positive control) and superiority (versus placebo control) trials were conducted. Patients with positive tests for the influenza virus (rapid detection of antigens to the influenza virus before enrollment, but if detection of nucleic acid of the influenza virus or cultivation of the influenza virus was inconsistent, the patient was excluded) were assigned randomly into three groups of equal proportions (1:1:1). Groups were: oseltamivir treatment (positive control), BLG granule treatment (test group) and placebo group. Patients will accept 5-day treatment and 21-day observation. Patient follow-up was undertaken on days 1, 3, 5, 7, 21 (Table 1 and Figure 1). Specific items that were collected for each follow-up period are outlined in Table 1.

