#### Placebo group

The placebo group will receive BLG analogous granules, twice a day, 30 min after eating, taken with an analogous oseltamivir phosphate capsule.

The BLG granules and the BLG analogous granules were produced according to the quality requirements of the *People’s Republic of China Pharmacopoeia* (Additional files 1 and 2)*.* Furthermore, the placebo includes white powdered sugar (41.1%), brown powdered sugar (22.6%), amylum (16.43%), dextrin (10.27%), caramel syrup (1.4%), and lemon yellow (8.2%).

All drugs were packaged by Hutchisom Whampoa Guangzhou Baiyunshan Chinese Medicine Company Limited (Guangzhou, China) according to the requirements of a double-blind, double-simulation test. The drugs used in this double-blinded trial were counted and sorted by a third party (Southern Medical University, China). All drugs were in the period of validity.

Other treatments for participants have to meet the standards for using other drugs, which are axillary temperature ≥38.5°C that continues more than 4 hours and does not degrade with physical cooling or body temperature is gradually raised ≥ 39°C. When these standards are met, the symptoms are treated as indicated: fever: paracetamol; white sputum, bromhexine; and mild asthmatic symptoms, long-term theophylline. With these exceptions, no other drugs can be used. Furthermore, detailed information on the drug use will be registered in the case report form (CRF).

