#### Primary outcome

The first primary outcome is the duration of the illness and will be measured in hours. Duration of illness is defined as the time from symptom onset to alleviation of the influenza-like symptoms: nasal obstruction, running nose, cough, sore throat, headache, fatigue, myalgia, chills and sweating. The definition of symptom alleviation is influenza-like symptoms score ≤1 (mild) and maintenance of stable symptoms for more than 24 h [30,32].

Another primary outcome is the time to defervescence, which is measured in hours. The time from the first dose of the study medication to the time when the body temperature decreases to <37.4°C is defined as ‘defervescence,’ and when it is sustained for ≥24 h, it is defined as ‘complete defervescence’ [30,32].

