#### Secondary outcome

Five secondary endpoints are being considered. The first is the duration of viral shedding. This endpoint is defined as the time from illness onset to the first time the viral nucleic acid test is negative. The second endpoint is disease severity. It is assessed by an area under the curve (AUC) analysis of nine influenza-like symptom scores [29]. The AUC is calculated as the product of the daily symptom scores multiplied by the duration of illness. The third endpoint is the frequency of acetaminophen usage. The fourth endpoint is the prevalence of secondary influenza complications. These are otitis, bronchitis, pneumonia, nasosinusitis, suppurative tonsillitis, acute parotitis, Reye’s syndrome, central nervous system disease, myocarditis, pericarditis, acute myositis, and toxic shock syndrome. The final endpoint was an economic evaluation.

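### The fever co-primary carries the name of the unsustained event, so a temporary fall after permitted paracetamol can count as defervescence

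*Protocol article*

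**What the plan says.** All references are to the protocol article.

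- **Named outcome (Primary outcome).** "Another primary outcome is the time to defervescence, which is measured in hours".
- **Its definition (same section).** Defervescence is "The time from the first dose of the study medication to the time when the body temperature decreases to <37.4°C". No duration is attached.
- **A second event (same sentence).** The fall is called complete defervescence "when it is sustained for ≥24 h".
- **The other primary outcome (same section).** Duration of illness ends at symptom alleviation, which requires "maintenance of stable symptoms for more than 24 h".
- **Secondary outcome.** "Five secondary endpoints are being considered". Sustained defervescence is not one of them. The frequency of acetaminophen use is.
- **Rescue (Drugs and usage, at the end of the Placebo group subsection).** Other drugs are allowed at "axillary temperature ≥38.5°C that continues more than 4 hours" despite physical cooling, or once temperature climbs to 39°C or more. Then "the symptoms are treated as indicated: fever: paracetamol". Details of drug use go into the case report form (CRF).
- **Design.** "Noninferiority (versus positive control) and superiority (versus placebo control) trials were conducted".

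**The concern.** Two different fever events are defined under one primary heading, and the primary outcome bears the name of the one without a persistence requirement. Paracetamol is allowed during the period in which fever is being timed, and the article does not link its use to the fever endpoint. Read literally, a patient whose temperature dips after a rescue dose and rises again has reached the primary event at the dip.

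Fever triggers rescue, so counted temporary falls are likely to be at least as frequent in the arm where the drug works less well. Recording those patients as early successes would tend to pull the arms together. Against placebo, that costs power for superiority. Against oseltamivir, it tends to make a less effective Ban-Lan-Gen (BLG) look closer to the control, which is the direction that favours noninferiority. Both comparisons are planned.

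With two candidate events and no stated choice, the article also does not prevent the event from being chosen after results are known.

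**Working it through.** **Step 1: which event is primary?** The article gives no figure to reproduce here, so the check starts with the text.

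| Item | Threshold | Persistence | Called primary? |
|---|---|---|---|
| Duration of illness | symptom score ≤1 | more than 24 h | yes |
| Defervescence | <37.4°C | none | yes, by name |
| Complete defervescence | <37.4°C | at least 24 h | not stated |

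The label of the primary outcome matches the middle row. Nothing in the article assigns the bottom row a role.

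**Step 2: can a paracetamol dip qualify?** The rescue thresholds are 38.5°C (persistent) and 39°C. To be counted, temperature must fall by more than:

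- 38.5 − 37.4 = 1.1°C, or
- 39.0 − 37.4 = 1.6°C,

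and a reading must catch it. This is possible, but it limits how many patients are affected.

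**Step 3: illustration of size.** The article gives no mean fever duration, rescue rate or effect size, so every input below except the arm size is an assumption.

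Notation: C is the weaker arm and A the better arm; p is the share with a counted temporary fall; m is the mean true time to lasting defervescence in those patients; d is the hour of the counted fall.

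Reduction in the mean difference = p_C(m_C − d) − p_A(m_A − d)

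*Case 1: affected patients have their arm's mean (48 h and 36 h, difference 12 h).*

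| p_C / p_A | d | Calculation | Reduction |
|---|---|---|---|
| 5% / 5% | any | 0.05 × 12 | 0.6 h (5%) |
| 20% / 20% | any | 0.20 × 12 | 2.4 h (20%) |
| 10% / 5% | 8 h | 0.10 × 40 − 0.05 × 28 | 2.6 h (22%) |
| 10% / 5% | 24 h | 0.10 × 24 − 0.05 × 12 | 1.8 h (15%) |
| 5% / 10% | 8 h | 0.05 × 40 − 0.10 × 28 | −0.8 h (difference widens) |
| 5% / 10% | 24 h | 0.05 × 24 − 0.10 × 12 | 0 h |

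With 177 / 3 = 59 patients per arm, 5–20% is about 3–12 patients per arm.

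The effect changes sign at p_A / p_C = (48 − d) / (36 − d): 40 / 28 = 1.43 at hour 8 and 24 / 12 = 2.0 at hour 24. Dilution therefore holds unless counted falls are more frequent in the better arm by more than that factor.

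*Case 2: affected patients have the same mean in both arms, for example 60 h.* Equal shares remove nothing. Shares of 10% and 5% remove 0.05 × (60 − 8) = 2.6 h at hour 8 and 0.05 × (60 − 24) = 1.8 h at hour 24.

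**The case against.** The strongest reply is that the sustained event was meant all along. It is defined under the primary heading, in the same sentence, and is not listed as secondary, so its definition has no other evident use. The companion outcome carries a 24 h rule, so the authors had persistence in mind. That is a fair reading, and it may be right. It does not settle the matter, because the article attaches the primary's name to the other event.

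A second reply is that this is a condensed article, and that the frequency of readings and the handling of readings after an antipyretic belong in the full protocol or analysis plan. That holds for those details, and their absence is not held against the plan. Which of two printed events is the primary outcome is different: the article itself creates that ambiguity.

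A third reply is that the route is narrow. Rescue needs high or persistent fever, the fall must be large and caught by a reading, and fever must then return. Drug use is recorded in the CRF, and acetaminophen frequency is analysed in its own right. All of this stands and limits how often the problem arises. It does not change what the definition counts.

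A fourth reply is that neither size nor direction can be computed from the document. This is also correct. Rescue selects patients with higher or longer fever, so giving them their arm's mean (Case 1) is doubtful; under Case 2, equal shares have no effect. The hours are an illustration, and the case for the change does not rest on them.

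Finally, duration of illness, the other primary outcome, is unaffected.

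**Conclusion.** The point holds and should be fixed. The article defines two fever events, gives the primary outcome the name of the unsustained one, and never says that the sustained one decides. As written, a temporary fall after permitted paracetamol meets a primary endpoint.

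Dilution of differences between arms is the likely direction but not a certain one. It rests on counted falls being at least as common in the weaker arm, or at least not much more common in the better arm. The illustrated effects run from a 0.8 h widening to a 2.6 h reduction of an assumed 12 h difference. They depend entirely on the assumed means, shares and timing, and cannot be turned into a loss of power or a noninferiority error from what the article gives. Confidence is medium, because the sustained event may be what the investigators intend to analyse.

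**What to change.** Before database lock and unblinding, name complete defervescence as the sole primary fever outcome: the time from first dose to the start of the first period of at least 24 h in which all readings are below 37.4°C. Report time to the first fall below 37.4°C as a supportive result.

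Optionally, if the drug-use entries in the CRF include paracetamol dose times, add a sensitivity analysis in which readings soon after a dose are not counted as afebrile. The article does not show whether dose times are recorded.

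**Cost.** This is a blinded clarification of a primary endpoint during the trial, to be documented as an amendment. By June 2014, 50 of 177 patients (28%) had finished (Trial status), and the Data management section places unblinding after database lock. The main change needs only temperature readings that either definition already requires. Patients whose fever does not return keep the same time. Overall, times will be slightly longer, and a few more patients may have no event by Visit 3 (Day 7 + 1 in Table 1). If the sustained event was always intended, the amendment simply records that.

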#### Secondary outcome

Five secondary endpoints are being considered. The first is the duration of viral shedding. This endpoint is defined as the time from illness onset to the first time the viral nucleic acid test is negative. The second endpoint is disease severity. It is assessed by an area under the curve (AUC) analysis of nine influenza-like symptom scores [29]. The AUC is calculated as the product of the daily symptom scores multiplied by the duration of illness. The third endpoint is the frequency of acetaminophen usage. The fourth endpoint is the prevalence of secondary influenza complications. These are otitis, bronchitis, pneumonia, nasosinusitis, suppurative tonsillitis, acute parotitis, Reye’s syndrome, central nervous system disease, myocarditis, pericarditis, acute myositis, and toxic shock syndrome. The final endpoint was an economic evaluation.

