**Table 1 Tab1:** **Follow-up chart of treatment using ban-lan-gen granules against seasonal influenza**

**Visit cycle evaluation projects**	**Screening stage**	**Remedial period**			
	**Visit 0 day 0.5 to 0**	**Visit 1 Day 3 + 1 after administration**	**Visit 2 Day 5 + 1 after administration**	**Visit 3 Day 7 + 1 after administration**	**Visit 4 Day 21 + 7 after administration**
Acquisition of basic medical history					
Informed consent	X				
Basic conditions	X				
Symptoms	X	X	X	X	
Inclusion and exclusion criteria	X				
Safety observations					
Vital signs	X			X	
Electrocardiography	X	a	a	X	
Chest radiograph	X	a	a	a	
Laboratory inspection	X	a	a	X	
Record adverse events	X	X	X	X	X
Efficacy					
Record influenza symptoms	X	X	X	X	
Virology					
Rapid diagnostic tests	X				
Real-time PCR analyses	X	X	X	X	
Viral isolation culture	X	X	X	X	
Viral antibody titer	X				X
Other					
Grouping and giving drugs	X				
Administer drugs	X	X	X		
Distribute patient diary card	X				
Accompanying treatment	A	A	a	a	
Compliance	X	X	X	X	
Inspection results	X				X
Original record completion	X	X	X	X	X
Recover study drug				X	
Recover patient diaries				X	
CRF review, recovering and test summary					X

X, must implement; a, necessary to implement.

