#### Statistical analyses

The software used for statistical analyses will be SPSS v17.0 (IBM, Armonk, NY, USA) or SAS v9.2 (SAS Institute, Cary, NC, USA).

All statistical inferences will be determined using two-sided tests. *P* <0.05 will be considered significant, and 95% confidence intervals will be used.

Efficacy analyses will use LOCF to compensate for cases not fully covered during treatment. The LOCF approach uses the last data observed, which is transferred to the database to obtain a complete dataset. The safety assessment will not evaluate missing data.

A comparison between the dropout rate and dropout rate caused by adverse events will be undertaken using the Pearson’s χ^2^test.

Data will be described as the mean, standard deviation, and confidence intervals. If necessary, minimum, maximum, P25, P75, and median values will be provided. Paired measurement data will also show the differences between the mean and standard deviation. When using nonparametric methods, median and mean values will be provided. Count data will be described using the frequency distribution and corresponding percentage. Data of concentrations will be described using the frequency distribution and the corresponding percentage, as well as median and average values. Qualitative information will be described using the positive rate, the number of positive cases, and the denominator.

Baseline data analyses (two sets) will include demographic indicators, as well as general, primary and secondary indicators before intervention. Measurement data will be described using a *t*-test or t’ test (if the variance is absent). Count data will be described using the Pearson’s χ^2^test. Rating data will be described using the two-sample Wilcoxon rank sum test.

With respect to analyses of effectiveness, for quantitative variables, comparisons between groups will be undertaken using repeated measures analysis of variance and covariance analysis. For qualitative variables, comparisons between groups will be tested using the Pearson’s χ^2^test, whereas center effect analysis will use CMH. For rating variables, comparisons between groups will be tested using the Kruskal-Wallis test, regression analysis center effect via the CMH test, or grade logistics.

In terms of center effect analyses, the GLM method will be used for quantitative indicators and CMH methods for qualitative indicators. Rating variables will be evaluated and corrected using a logistic regression model.

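### Duration of viral shedding ends at one unconfirmed negative PCR and is seen only at Days 3, 5 and 7; the article's general rule would treat this censored time as complete, which biases the between-arm difference, usually but not always toward no effect

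*Protocol article*

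**What the plan says.** The protocol article, Secondary outcome, lists duration of viral shedding first among five secondary endpoints and defines it so: "This endpoint is defined as the time from illness onset to the first time the viral nucleic acid test is negative". It asks for no second negative and does not say what happens if a later swab is positive. The Primary outcome section does ask for persistence: alleviation of symptoms requires "maintenance of stable symptoms for more than 24 h", and complete defervescence has a 24-hour rule too.

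In Table 1 the row "Real-time PCR analyses" is marked at screening and at three visits after dosing: "Visit 1 Day 3 + 1 after administration", "Visit 2 Day 5 + 1 after administration" and "Visit 3 Day 7 + 1 after administration". It is blank at the Day 21 visit.

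The Statistical analyses section sorts efficacy variables into quantitative, qualitative and rating. For the quantitative class, "comparisons between groups will be undertaken using repeated measures analysis of variance and covariance analysis". On incomplete data: "Efficacy analyses will use LOCF to compensate for cases not fully covered during treatment", with the stated aim of a dataset without gaps. The section names no time-to-event or censoring method, and it does not mention viral shedding individually.

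**The concern.** With this schedule nobody's clearance time is observed. A patient's clearance lies before the Day 3 swab, between two swabs, or after the Day 7 swab. In the last case the definition yields no value, because no negative test ever occurs. A duration fits neither the qualitative nor the rating class, so the rule for quantitative variables is the one that would apply. That rule needs one complete number per patient, and the missing numbers belong mostly to the arm that clears more slowly.

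The single-negative rule is a separate fault. A false negative at Day 3 fixes the endpoint at Day 3 even if Days 5 and 7 are positive.

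The Background and Discussion rest the case for the herb on antiviral action, and the results of this pilot are to inform a large-scale trial. A distorted virological difference would carry forward into that trial.

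**Working it through.** The article gives no figure for shedding to reproduce. Its only design figure is 177 patients, or 177/3 = 59 per arm. The size of the bias therefore rests on assumptions, shown as a range.

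**Inputs.** From Table 1: swabs at Days 3, 5 and 7, ignoring the +1 windows. Assumed: log-normal time from first dose to clearance, median m of 3 to 6 days, log-SD s of 0.3 or 0.5. The interval from onset to first dose (up to 36 h under the inclusion criteria) has the same expectation in each arm by randomisation, so it cancels from the difference in means.

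**Step 1, perfect tests.** With F(t) = Φ(ln(t/m)/s), the four observable cells are p0 = F(3), p1 = F(5) − F(3), p2 = F(7) − F(5), p3 = 1 − F(7).

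- True mean: m·exp(s²/2).
- Day 7 positives dropped: (3p0 + 5p1 + 7p2)/(1 − p3).
- Day 7 positives set to 7: 3p0 + 5p1 + 7(p2 + p3).

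Example, s = 0.5. For m = 5 the cells are 0.153, 0.347, 0.250, 0.250; for m = 4 they are 0.283, 0.390, 0.196, 0.132. True difference: (5 − 4)·exp(0.125) = 1.133. Dropped: 5.256 − 4.801 = 0.455. Set to 7: 5.693 − 5.090 = 0.603 (means from unrounded cells).

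| Medians (days) | log-SD | Positive at Day 7 | True difference | Dropped | Set to 7 |
|---|---|---|---|---|---|
| 5 v 4 | 0.5 | 25% v 13% | 1.133 | 0.455 (60% lost) | 0.603 (47% lost) |
| 5 v 4 | 0.3 | 13% v 3% | 1.046 | 0.688 (34% lost) | 0.792 (24% lost) |
| 6 v 5 | 0.5 | 38% v 25% | 1.133 | 0.325 (71% lost) | 0.426 (62% lost) |
| 4 v 3 | 0.3 | 3% v 0.2% | 1.046 | 0.977 (7% lost) | 1.031 (1% lost) |

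**Step 2, false negatives.** Let f be the chance that a swab reads negative during shedding. Falsely called cleared: p1·f + p2·(1 − (1 − f)²) + p3·(1 − (1 − f)³). At s = 0.5:

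- m = 6, f = 0.10: 0.275×0.10 + 0.263×0.19 + 0.379×0.271 = 0.180. With f = 0.05: 0.093.
- m = 4, f = 0.10: 0.390×0.10 + 0.196×0.19 + 0.132×0.271 = 0.112. With f = 0.05: 0.057.

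Under a rule of no later positive, only a false negative at the last swab taken during shedding survives: f·(p1 + p2 + p3). At f = 0.10 this is 0.092 for m = 6 (49% removed) and 0.072 for m = 4 (36% removed).

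**Step 3, direction.** In 42 simulated scenarios with log-SD 0.3 to 0.5, false negatives equal in both arms and Day 7 positives set to 7, the observed difference was 0.22 to 0.99 of the true one. Two other settings went the opposite way. With medians 5.2 v 4.8 days and log-SD 0.05 to 0.10, no false negatives, a true 0.40 days became 0.62 to 1.16, because the swab grid splits the arms. With no true effect but 25% false negatives on the active arm against 5% on placebo, about 0.7 days appeared in favour of treatment.

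**Step 4, what the remedy recovers.** Simulation with 59 per arm, medians 5 v 4, log-SD 0.5, true time ratio 0.80. The remedy was an interval-censored model with each negative confirmed at the next scheduled swab, a close relative of the rule proposed below.

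| False negatives | Power, single negative, ANOVA, Day 7 cap | Power, interval-censored, confirmed | Estimated ratio after remedy |
|---|---|---|---|
| 0% | 0.61 | 0.63 | 0.80 |
| 10% | 0.44 | 0.53 | 0.81 |
| 20% | 0.26 | 0.49 | 0.81 |

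Without false negatives, the interval-censored model on single negatives had power 0.64 against 0.61. Censoring alone distorts the estimated difference more than the power; most of the power loss comes from unconfirmed negatives.

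**The case against.** The strongest reply is that much of this is inferred. The article does not assign a method to viral shedding, it allows for nonparametric methods elsewhere, and a statistical analysis plan that is not shown may set censoring rules. LOCF is directed at patients not fully covered during treatment; one who attends every visit and is positive at Day 7 has missed nothing. A reader might infer that the plan drops such patients or sets them to Day 7. It says neither, and both are assumptions of the calculation. This stands, and it limits how firmly the analysis can be faulted. It does not touch the single-negative rule, the swab schedule, or the absence of a value for Day 7 positives, which are explicit.

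A reader might also infer that the design shrinks any antiviral effect. The last two cases in Step 3 refute that. Nor is PCR the only virological measurement: Table 1 also schedules viral culture at the same visits, although Secondary outcome does not name it as an endpoint.

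Finally, the size depends on medians, spread and swab sensitivity that the documents do not give, and it can be close to nil. That is correct, and it is why a range is shown.

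**Conclusion.** The point holds in limited form. The endpoint as defined is interval-censored and right-censored, and one unconfirmed negative can end it early. Under the only rule the article gives for quantitative efficacy variables it would be handled as complete. The resulting bias is usually toward no effect, but it can run the other way.

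With medians 5 v 4 days, roughly a quarter to three fifths of the true difference is lost, depending on log-SD and on how Day 7 positives are handled. Early clearance with little spread costs almost nothing. False clearance of about 6 to 18% assumes sensitivity 0.90 to 0.95, log-SD 0.5 and medians 4 to 6 days.

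This is one of five secondary endpoints. Neither primary outcome nor the sample size of 177 is affected. It should be corrected, but it does not undermine the trial.

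**What to change.** - Define clearance as the first negative PCR with no positive at any later scheduled swab.
- Keep illness onset as the time origin; a change to first dose would be a different endpoint.
- Analyse the interval from last positive to first sustained negative as interval-censored, using actual swab times because of the +1 windows. Right-censor patients still positive at the Day 7 visit.
- State that LOCF does not apply to this endpoint.
- Report the proportion PCR-negative at Days 3, 5 and 7 by arm alongside.

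The cost is endpoint and analysis wording only: no extra swabs or patients. Trial status reports 50 patients finished by June 2014, and Data management places unblinding after database lock, so the change can be made while blinded.

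Two limits remain. A first negative at Day 7 cannot be confirmed and should be flagged. The rule also removes only part of the false clearances, about 35 to 50% in the settings of Step 2, because an early false negative followed by true clearance before the next swab still counts.
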